## Abstract

**Introduction:**

Major depressive disorder (MDD) is a prevalent psychiatric condition associated with significant suicide risk. Sequential accelerated theta-burst stimulation (aTBS), which integrates time-efficient stimulation with sequential modulation of multiple targets, represents a promising neuromodulation strategy. However, the efficacy and safety of sequential aTBS in adults with MDD and active suicidal ideation remain unexplored. This study aims to evaluate the therapeutic safety and effect of sequential aTBS on suicidal ideation in adults with MDD, and to explore its associated neurophysiological mechanisms using electroencephalography-derived P300 event-related potentials.

**Methods and analysis:**

This study is a single-blind, randomized controlled trial. Fifty-six adults with MDD will be recruited and randomly assigned (1:1) to receive either active sequential bilateral Dorsolateral Prefrontal Cortex (DLPFC) aTBS (10 weekday sessions; 3600 pulses per session) consisting of continuous theta-burst stimulation (cTBS) applied to the right DLPFC followed by intermittent theta-burst stimulation (iTBS) applied to the left DLPFC, or sham stimulation. The primary outcomes will be response and remission rates based on the 17-item Hamilton Depression Rating Scale (HAMD-17). Secondary outcomes will include the Beck Depression Inventory-II (BDI-II), the Columbia Suicide Severity Rating Scale (C-SSRS), and electroencephalography (EEG)-derived electrophysiological markers of cognitive processing (P300). Safety and tolerability will be systematically evaluated throughout the study using the Treatment Emergent Symptom Scale (TESS) to record stimulation-related adverse events. Outcome measures will be assessed at baseline, immediately after the 10-day intervention, and at 2-week and 4-week follow-ups to evaluate the short-term sustainability of treatment effects.

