### Objectives

The primary objective of this randomized controlled trial is to evaluate the clinical efficacy of sequential accelerated Theta Burst Stimulation (aTBS) in adults with MDD. Our central hypothesis is that, compared to sham stimulation, sequential aTBS will induce a faster and more significant alleviation of depressive symptoms, with this therapeutic effect remaining significant throughout the subsequent 2-week and 4-week follow-up periods. A secondary objective of this study is to systematically evaluate the safety, tolerability, and adverse event profile of sequential aTBS in the target population. For this safety assessment, the Treatment Emergent Symptom Scale (TESS) will be administered to capture and characterize common adverse events, including headache, dizziness, nausea, scalp discomfort, and muscle twitching. For mechanistic exploration, this study will employ high-temporal-resolution EEG to capture the P300 event-related potential as a neurophysiological indicator, aiming to elucidate the mechanisms by which aTBS modulates cortical excitability and cognitive-emotional processing, thereby identifying potential biomarkers for future treatment strategies.

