**Figure 1 f1:**
[figure not shown]
CONSORT flow diagram of the study protocol; Patient screening; Depressed patients (n=56); Randomized allocation; Active stimulation group (n=28); Sham stimulation group (n=28); T0, baseline (randomization); T1, post-intervention; T2, 2-week follow-up; T3, 4-week follow-up; HAMD-17, 17-item Hamilton Depression Rating Scale; BDI-II, Beck Depression Inventory-II; C-SSRS, Columbia-Suicide Severity Rating Scale; aTBS, accelerated theta-burst stimulation.

**Table 1 T1:** Detailed trial schedule.

	Study period							
	Enrollment	Allocation	Post-allocation				Follow-up 1	Follow-up2
Time point	Day-1	Day 0	AFT	Day1	~	Day 10 (Intervention period)	Week2	Week4
Enrollment:								
Eligibility screen	×							
Informed consent	×							
Randomization	×							
Allocation		×						
Interventions:								
Conventional treatment + sequential aTBS								
Conventional treatment + sham sequential aTBS								
Assessments:								
HAMD-17		×				×	×	×
BDI-II		×				×	×	×
C-SSRS		×				×	×	×
P300		×				×		
Case report forms	×							
Adverse events								
TESS								
Blinding			×					
TASS	×							
ATHF	×							

AFT; Immediately post-allocation (after randomization and before the first intervention); HAMD-17, 17-item Hamilton Depression Rating Scale; BDI-II, Beck Depression Inventory-II; C-SSRS, Columbia-Suicide Severity Rating Scale; P300, Electroencephalography; ATHF, Antidepressant Treatment History Form; TASS, Transcranial Magnetic Stimulation Safety Screen; TESS, Treatment Emergent Symptom Scale ×, occurs at that time.

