### Study outcomes

#### Primary outcome

The primary outcome is to compare the response rate of depressive symptoms between the active stimulation group and the sham stimulation group after intervention. The response rate is defined as a reduction of 50% or more in the HAMD-17 score compared with the baseline. Remission is defined as a HAMD-17 score of ≤ 7 (32).

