### Statistical analysis

#### Sample size

The sample size for this exploratory trial was determined *a priori* using G*Power software (version 3.1). An F-test was employed based on an effect size (Cohen’s d) of 0.38 by Chu et al. (2021). A total of 50 participants were required to achieve 80% statistical power at a two-sided alpha level of 0.05 (37). Anticipating an approximate dropout rate of 10%, the planned enrollment was at 56 participants.

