#### Analysis of clinical data

All statistical analyses will be conducted using SPSS version 26.0. Continuous variables will be presented as means ± standard deviations or medians (interquartile ranges), depending on distribution, and compared using independent samples t-tests or Mann-Whitney U tests, as appropriate. Categorical variables will be expressed as frequencies (%) and analyzed using Chi-square or Fisher’s exact tests. A repeated-measures analysis of variance (ANOVA) will be applied to evaluate longitudinal changes in each outcome, with group (active vs sham) as the between-subject factor and time (baseline, post-intervention, follow-up) as the within-subject factor. If the assumption of sphericity is violated according to Mauchly’s test, the Greenhouse-Geisser correction will be applied. Significant interactions will be followed by Bonferroni-adjusted simple-effects comparisons to determine between-group differences at each time point and within-group changes across time.

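### Remission is a primary outcome in the abstract but has no assigned role in the outcomes section, and no stated adjustment covers the tests of the two rates

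*Protocol article*

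**What the plan says.** The abstract of the protocol article, under Methods and analysis, uses the plural: "The primary outcomes will be response and remission rates based on the 17-item Hamilton Depression Rating Scale (HAMD-17"). The Primary outcome section uses the singular: "The primary outcome is to compare the response rate of depressive symptoms between the active stimulation group and the sham stimulation group after intervention". The same paragraph then adds "Remission is defined as a HAMD-17 score of ≤ 7", with no comparison and no rank attached. The section on secondary clinical outcomes covers the C-SSRS and the BDI-II and does not mention remission.

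On timing, the legend of Figure 1 reads "T1, post-intervention; T2, 2-week follow-up; T3, 4-week follow-up", so the comparison after intervention is the one at T1. The Objectives section expects an effect at the end of treatment, "with this therapeutic effect remaining significant throughout the subsequent 2-week and 4-week follow-up periods".

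On testing, the section Analysis of clinical data says "Categorical variables will be expressed as frequencies (%) and analyzed using Chi-square or Fisher’s exact tests". For the repeated-measures ANOVA it says "Significant interactions will be followed by Bonferroni-adjusted simple-effects comparisons to determine between-group differences at each time point". The only significance level appears in the sample-size paragraph: "A total of 50 participants were required to achieve 80% statistical power at a two-sided alpha level of 0.05".

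**The concern.** Which outcome is primary is a matter this article does fix, and it fixes it in two incompatible ways. An analysis plan that is not shown could add detail, but it could not make both statements true. A reader of the abstract would accept a significant remission rate as a primary success; a reader of the outcomes section would not.

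With the role of remission open, the choice could be made after the data are seen. If response and remission are each tested at 0.05 and either is allowed to carry the conclusion, the chance of a false positive exceeds the level of a single test. Both rates are cut-points on the same clinician-rated scale. The Blinding section says that those who assess outcomes know the allocation. That is a separate issue, but it makes a fixed endpoint more valuable.

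**Working it through.** **Inputs from the article.** Two-sided alpha 0.05; 50 evaluable patients; 10% dropout; 1:1 allocation; HAMD-17 of at least 17 at entry; response is a fall of at least 50%; remission is a score of 7 or less.

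**The plan's own figure.** 50 / (1 − 0.10) = 55.6, rounded up to 56, which agrees. This gives 25 evaluable or 28 enrolled per arm. The article states no overall error rate for the primary claim, so there is none to reproduce.

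**How the two outcomes relate.** A patient who enters at 17 and reaches 7 has fallen by 10/17 = 59%, and a higher entry score gives a larger fall. So with a baseline of at least 17, every remitter is also a responder. The two tests are positively related but not identical.

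**Simple reference values, if either may win.** For independent tests at 0.05 each, 1 − 0.95² = 9.75%. With 0.025 each, 1 − 0.975² = 4.94%, and the Bonferroni bound is 5%.

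**Simulation with no treatment effect.** Assumptions that are not in the article: baseline HAMD-17 about 22 (SD 3.5, minimum 17), response 32–65%, remission 14–40%, between-visit correlation 0.4–0.7. Both rates come from the same score; 20,000 trials were run per setting.

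| Rule at T1 | Chi-square, uncorrected | Fisher's exact |
|---|---|---|
| Response only | 4.4–6.5% | 2.2–3.3% |
| Response or remission, 25 per arm | 9.3–10.4% | 3.7–5.0% |
| Response or remission, 28 per arm | 8.1–9.2% | 3.7–5.0% |

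Some chi-square values pass 9.75% because the uncorrected test is itself slightly liberal at this size, as the first row shows.

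**Using both tests.** The article allows either test and gives no rule for choosing. A common convention, assumed here, is Fisher's test when an expected count is below 5. With 25 per arm the expected number of remitters per arm is 25 × p, which is below 5 when p is below 0.20. Remission would then be tested by Fisher's test when it is rare and by chi-square when it is not. A second simulation (25 per arm, assumed response 18–64%, remission 7–36%) gave, for response or remission at T1:

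- chi-square throughout: 8–10%
- Fisher's test when an expected count is below 5: 4–10%
- Fisher's test throughout: 2.5–5%

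**Follow-up visits.** The Objectives ask for an effect that persists, so success would need significance at T1, T2 and T3 together. In the first simulation that happened by chance in at most about 0.5% of trials for response, and at most about 0.8% when either rate could start the claim at T1. Requiring persistence lowers the error.

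**The case against.** The strongest reply is that this is a wording slip in an abstract. The Primary outcome section names one outcome and one time, the article calls the trial exploratory, and an alpha split or decision rule commonly sits in an analysis plan that is not shown. No passage says that either rate may win. With Fisher's test, which the article permits, even that rule stays at about 5%.

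Much of this stands. The inflation is conditional on an unstated rule and on the test used, and the absence of a detailed multiplicity procedure is not itself the fault. What does not fall away is the contradiction: the abstract assigns remission primary status, and the body neither repeats that nor makes remission secondary. Calling the trial exploratory does not settle which statement holds.

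A reader might also infer that the hypothesis opens two further visits as chances to succeed, giving six tests (two rates at three visits). Simulated error for any one of six is 20–27% with chi-square and 9.6–13.7% with Fisher's test. The documents do not support that reading: the primary comparison is placed after intervention, the hypothesis is a joint condition, and no passage states an any-of-six rule. Nor is it right that error control is absent altogether, since the ANOVA comparisons at each time point are Bonferroni-adjusted after a significant interaction. That control covers the ANOVA follow-up and leaves the tests of the two rates outside it.

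**Conclusion.** The concern holds as a contradiction about the primary endpoint, with a conditional effect on the error rate. The abstract has two primary outcomes and the outcomes section has one; remission's role is undefined; and the stated adjustment does not reach the tests of these rates. The contradiction is certain from the text. The size is not. It is about 8–10% with chi-square, about 4–10% with Fisher's test for small expected counts, and at most about 5% with Fisher's test throughout. All three assume that either rate may carry the trial at 0.05 and rest on assumed response and remission rates. The follow-up visits add nothing to it.

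**What to change.** State the same thing in the abstract and in the Primary outcome section: one primary outcome, HAMD-17 response at T1, compared between groups at two-sided 0.05. List remission at T1 and the T2 and T3 results as secondary. Do this before outcomes are compared by group, and check that the registry entry, which is not available here, agrees.

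If both rates are to remain primary, say which rule applies. If both must succeed, each can be tested at 0.05. If either may succeed, test each at 0.025.

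The cost is a few sentences. With a single primary, remission alone can no longer carry the trial. The alpha split costs power: for illustrative response rates of 20% and 50% with 25 per arm (assumed, not from the article), power falls from about 61% at 0.05 to about 49% at 0.025.

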**Discussion:**

The results of this study will provide information regarding the efficacy and safety of sequential aTBS for MDD, evaluating its feasibility and thereby laying a foundation for future clinical interventions and scientific research.

**Clinical Trial Registration:**

https://www.medicalresearch.org.cn/index, identifier ChiCTR2500109181.

## Introduction

Major depressive disorder (MDD) is a highly prevalent mental health condition in adults, characterized by a lifetime prevalence of 10%-15%, high relapse rates, and particularly severe suicide risk. Suicide remains one of the leading causes of mortality among adults worldwide (1). The central clinical challenge involves suicidal ideation, which affects approximately 60%-80% of adult patients (2). Despite its severity, currently available pharmacological and psychotherapeutic treatments remain limited in their ability to provide rapid stabilization. Antidepressant medications require weeks to exert therapeutic effects, making them unsuitable for acute risk management, while high relapse rates frequently lead to the re-emergence of suicidal ideation even after initial improvement (3, 4). Therefore, there is an urgent need for rapid-acting, safe, and evidence-based interventions specifically targeting suicidal ideation in adults with MDD.

Transcranial magnetic stimulation (TMS) is an FDA-approved intervention for depression, valued for its non-invasiveness, favorable safety profile, and clinical utility (5). The conventional 10-Hz left Dorsolateral Prefrontal Cortex (DLPFC) protocol, however, requires a 6-week course and yields modest response and remission rates (29%–46% and 18%–32%), with treatment burden contributing to substantial dropout (6, 7). These limitations have accelerated the search for more time-efficient neuromodulation strategies. Theta-burst stimulation (TBS) offers a condensed, time-efficient alternative: intermittent theta-burst stimulation (iTBS) increases cortical excitability when applied to the left DLPFC, whereas continuous theta-burst stimulation (cTBS) suppresses hyperactivity in the right DLPFC, with both forms capable of inducing rapid neuroplastic changes (8–10). The 2022 FDA clearance of the Stanford Accelerated Intelligent Neuromodulation Therapy (SAINT) protocol—which consists of 10 daily sessions, each delivering 1,800 pulses with a 50-minute inter-session interval over five consecutive days, totaling 90,000 pulses, and is characterized by individualized functional-connectivity targeting and high-dose, short-interval stimulation—highlighted the clinical feasibility of accelerated theta-burst stimulation (aTBS) paradigms (11). Subsequent clinical studies have demonstrated that SAINT produces rapid antidepressant effects and high remission rates in treatment-resistant depression (12). In addition, recent studies have shown that accelerated cTBS and iTBS interventions can effectively alleviate suicidal ideation in patients with treatment-resistant depression (13). An independent study focusing on iTBS also confirmed that this therapy significantly improved suicidal ideation among such patients (14). Nevertheless, existing aTBS paradigms remain largely restricted to single-target stimulation, leaving critical questions about stimulation sequences and network-level modulation unresolved.

Based on these considerations, sequential aTBS has emerged as a novel TMS strategy. It integrates high-intensity, short-interval theta-burst stimulation with sequential modulation of multiple cortical targets. This design enables a single treatment session to produce synergistic excitatory and inhibitory effects, forming an “excitation-inhibition-regulation” circuit that may enhance the plasticity of large-scale brain networks (15). Compared to the SAINT protocol, sequential aTBS is designed to reduce per-session stimulation intensity and overall treatment burden by distributing neuromodulatory effects across multiple cortical targets. By stimulating multiple functionally connected brain regions—typically the excitatory left DLPFC and the inhibitory right DLPFC—it promotes interhemispheric balance and accelerates emotional regulation. Theoretically, this multi-target approach aligns with the contemporary understanding of “depression as a network disorder” as MDD pathogenesis is associated with dysfunction in the prefrontal-limbic circuitry (16).

Current evidence regarding sequential accelerated theta-burst stimulation (aTBS) for the treatment of depression remains limited. Existing studies have primarily involved adults with treatment-resistant depression, including naturalistic observational studies of bilateral sequential aTBS targeting the dorsolateral prefrontal cortex (15), or have been confined to protocol designs for adolescents with major depressive disorder accompanied by suicidal ideation (17). Notably, these studies are characterized by heterogeneous clinical endpoints and involve populations such as adolescents, highly treatment-refractory individuals, or mixed groups with various depressive disorders. To date, no randomized controlled trial has specifically investigated sequential bilateral aTBS in adults with MDD who present active suicidal ideation.

Growing evidence suggests that suicidal ideation in MDD patients is associated with impairments in cognitive control, attentional regulation, and emotional processing, primarily involving the prefrontal-limbic circuitry (18, 19). Investigating these neurophysiological mechanisms may provide objective biomarkers for identifying suicide risk and evaluating treatment efficacy. Electroencephalography (EEG), with its high temporal resolution, enables direct assessment of cortical excitability and cognitive dynamics under neuromodulation. Among EEG-derived event-related potentials, the P300 component—typically elicited by an auditory oddball paradigm—serves as a reliable indicator of attentional resource allocation and information processing (20, 21). Consistent evidence shows reduced P300 amplitude and prolonged latency in depressed patients, reflecting diminished cognitive efficiency and prefrontal dysfunction (22). Moreover, effective antidepressant interventions—including high-frequency repetitive transcranial magnetic stimulation (rTMS)—have been shown to normalize P300 parameters in parallel with clinical improvement (23). These findings support the use of P300 as a sensitive electrophysiological marker of treatment response. Therefore, evaluating P300 changes before and after sequential aTBS may provide crucial insights into the neurophysiological mechanisms underlying its therapeutic effects, thereby helping to elucidate the intervention’s neurophysiological principles of action.

### Objectives

The primary objective of this randomized controlled trial is to evaluate the clinical efficacy of sequential accelerated Theta Burst Stimulation (aTBS) in adults with MDD. Our central hypothesis is that, compared to sham stimulation, sequential aTBS will induce a faster and more significant alleviation of depressive symptoms, with this therapeutic effect remaining significant throughout the subsequent 2-week and 4-week follow-up periods. A secondary objective of this study is to systematically evaluate the safety, tolerability, and adverse event profile of sequential aTBS in the target population. For this safety assessment, the Treatment Emergent Symptom Scale (TESS) will be administered to capture and characterize common adverse events, including headache, dizziness, nausea, scalp discomfort, and muscle twitching. For mechanistic exploration, this study will employ high-temporal-resolution EEG to capture the P300 event-related potential as a neurophysiological indicator, aiming to elucidate the mechanisms by which aTBS modulates cortical excitability and cognitive-emotional processing, thereby identifying potential biomarkers for future treatment strategies.

## Materials and methods

### Study design

This randomized, sham-controlled clinical trial was approved by the Ethics Committee of Wuxi Mental Health Center and prospectively registered in the Chinese Clinical Trial Registry (ChiCTR; official website: www.chictr.org.cn, Registration No.: ChiCTR2500109181). All procedures will adhere to the principles of the Declaration of Helsinki and the Guidelines for Good Clinical Practice (GCP). Reporting will follow the SPIRIT 2025 recommendations, and the completed SPIRIT checklist is available in **Supplementary Material S1**.

This trial will be conducted at Wuxi Mental Health Center between September 2025 and August 2027. The assessment and screening will be conducted by two practicing physicians from Wuxi Mental Health Center. Eligible participants will be randomly allocated (1:1) to receive either active sequential accelerated theta burst stimulation (aTBS; 3,600 pulses per session, 10 sessions total) or sham stimulation. Outcome measures will include the 17-item Hamilton Depression Rating Scale (HAMD-17) (24), Beck Depression Inventory (BDI-II) (25), Columbia Suicide Severity Rating Scale (C-SSRS) (26), Treatment Emergent Symptom Scale (TESS) (27) and event-related potential P300. All assessments will be administered at baseline (T0), immediately after the final stimulation session (T1), and at 2-week (T2) and 4-week (T3) follow-ups. A detailed flow diagram of the trial is shown in **Figure 1**, and the trial schedule is presented in **Table 1**.

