Participants in the active group receive sequential bilateral aTBS twice daily for 10 treatment days. The interval between the two daily treatment sessions in this study is set at 3 hours This interval is based on the following considerations: (1) Safety: Drawing on experience from the SAINT protocol, a 3-hour interval provides sufficient safety redundancy (12); (2) Neurophysiological recovery: This interval allows the nervous system to recover from each stimulation session, avoiding excessive cumulative effects (30); (3) Tolerability: It reduces fatigue and discomfort, thereby improving treatment adherence. The aTBS protocol, illustrated in **Figure 2**, consists of cTBS applied to the right DLPFC followed immediately by iTBS applied to the left DLPFC. Specifically, cTBS delivers 1,800 pulses over 120 seconds, whereas iTBS consists of three trains of 600 pulses (3 minutes and 9 seconds each) separated by 10-second intervals, totaling 1,800 pulses over 570 seconds. The coil is positioned tangentially to the scalp with the handle pointing posterior–laterally at approximately 45°. Sham stimulation will be delivered by tilting the coil 90° away from the scalp, while maintaining identical stimulation targets, treatment duration, and procedural protocols to those of the active intervention. This sham stimulation protocol is widely accepted and utilized in clinical trials (31).

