#### Adverse events

All adverse events (AEs) will be systematically monitored and documented throughout the trial. For each AE, the occurrence time, severity, duration, clinical management, and outcome will be recorded, along with the investigator’s judgment of its relationship to the intervention. Serious Adverse Events (SAEs) will be defined as events resulting in death, life-threatening conditions, hospitalization or prolonged hospitalization, or significant functional disability. Any SAE will be reported immediately to the institutional ethics committee in accordance with regulatory requirements.

Given the established safety profile of transcranial magnetic stimulation, expected AEs include mild and transient symptoms such as scalp discomfort, headache, facial muscle twitching, dizziness, or fatigue. Rare but potential risks (e.g., induction of seizure) will be communicated to participants during the informed-consent process (39). If any AE occurs, appropriate clinical management will be provided, and participants will be followed until symptom resolution or stabilization.

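### The P300 schedule contradicts itself; if Table 1 governs, the single post-treatment EEG follows straight after a session and mixes its acute after-effect with the effect of the course

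*Protocol article*

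**What the plan says.** The Study design section lists the outcome measures, ending with "Treatment Emergent Symptom Scale (TESS) (27) and event-related potential P300", and then fixes the visits for all of them: "All assessments will be administered at baseline (T0), immediately after the final stimulation session (T1), and at 2-week (T2) and 4-week (T3) follow-ups". The Abstract gives a similar timetable without naming the last session: "Outcome measures will be assessed at baseline, immediately after the 10-day intervention, and at 2-week and 4-week follow-ups". Table 1 differs for one measure. Its P300 row carries two marks (Day 0 and Day 10), while the rows for HAMD-17, BDI-II and C-SSRS carry four (Day 0, Day 10, Week 2 and Week 4).

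On spacing, the aTBS protocol section says: "The interval between the two daily treatment sessions in this study is set at 3 hours". It gives three reasons: safety, recovery and tolerability. The second reads: "This interval allows the nervous system to recover from each stimulation session, avoiding excessive cumulative effects". No minimum delay between the last session and the T1 EEG is stated.

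On purpose, the Introduction says that "evaluating P300 changes before and after sequential aTBS may provide crucial insights into the neurophysiological mechanisms underlying its therapeutic effects". The Objectives and the Discussion look to P300 for potential biomarkers. The limitations paragraph of the Discussion describes the EEG analysis as exploratory and not able to support causal inference.

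**The concern.** A before-and-after P300 comparison is meant to show what a course of treatment has done. Here the baseline recording is made in an unstimulated state and the T1 recording in a just-stimulated one. The protocol's own reasoning implies that these states differ: it spaces sessions partly for recovery, the Introduction says both forms of theta-burst stimulation can induce rapid neuroplastic change, and the Adverse events section says that "expected AEs include mild and transient symptoms such as scalp discomfort, headache, facial muscle twitching, dizziness, or fatigue". Dizziness, headache or fatigue could plausibly affect a button-press attention task.

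The sham arm does not remove the problem. Its coil is tilted 90° away from the scalp, so an after-effect of real stimulation is expected only in the active arm. With no later P300, a difference at T1 could come from the last session alone, or a transient opposite shift could hide a lasting change. Either would mislead the search for a marker of treatment response.

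**Working it through.** There is no figure in the plan to reproduce. The check sets the schedule statements side by side and then asks what the P300 contrast can estimate.

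**1. Post-treatment time points by measure**

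| Measure | Study design text | Table 1 |
|---|---|---|
| P300 | 3 (T1, T2, T3) | 1 (Day 10) |
| HAMD-17, BDI-II, C-SSRS | 3 | 3 (Day 10, Week 2, Week 4) |

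The text and the table agree for the ratings and disagree for P300.

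**2. Delay from last session to EEG.** The text gives no number and places T1 directly after the session. The P300 sections add 5–10 minutes of quiet sitting and 20–30 practice trials. At the longest stated timing (1.5 s interval plus 0.1 s tone), 30 trials take 30 × 1.6 = 48 s. The stated steps therefore account for at most about 11 minutes, plus cap placement, for which no time is given. The between-session interval is 3 hours, or 180 minutes.

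**3. What the contrast estimates.** Let *L* be the effect of the course on P300 and *a* the acute after-effect of the last session, present in the active arm only. With two time points, the group-by-time term of the planned repeated-measures ANOVA is

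(active T1 − active T0) − (sham T1 − sham T0) = *L* + *a*.

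This is one equation with two unknowns, so no analysis of Day 0 and Day 10 alone can separate them. If P300 is also recorded at T2 and T3, the same contrast at those visits shows what persists at 2 and 4 weeks without *a*. For the ratings this is already so under both schedules.

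**4. Illustration of size (assumed values).** Suppose *L* = 0 and *a* is 0.2, 0.3 or 0.5 SD. The documents supply none of these values. For a two-sample t-test at two-sided 5%, the noncentrality is *a* × √(n/2).

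- n = 25 per arm (half of the 50 required): √12.5 = 3.536, so noncentrality is 0.71, 1.06 and 1.77. The probability of a significant difference is 10.7%, 18.0% and 41.0%.
- n = 28 per arm (half of the 56 enrolled): √14 = 3.742, so noncentrality is 0.75, 1.12 and 1.87. The probability is 11.4%, 19.7% and 45.1%.

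These figures are simply the power of a t-test at assumed shifts, and the t-test is a simplification of the planned ANOVA. They show how often a purely acute shift would be reported as a P300 difference. If instead *a* = −*L*, the contrast is zero and a real lasting effect is hidden.

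**The case against.** Four stronger readings are tempting, and the documents do not support them.

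- **That T1 is outright the only post-treatment P300.** This follows from Table 1 alone. The Study design text, read literally, schedules P300 at T2 and T3 as well, and under that reading lasting change can be examined.
- **That the T1 ratings are equally uninterpretable.** They are not. HAMD-17, BDI-II and C-SSRS are repeated at Weeks 2 and 4 in both places, and the Objectives state a hypothesis about those visits. An acute effect could still touch the T1 rating itself, but later ratings exist to check it.
- **That 3 hours is a recognised washout.** It is a between-session interval, justified also by safety and tolerability. The protocol does not say how long after-effects last, so neither 3 hours nor a day is shown to clear them.
- **That the type I error is inflated.** A shift caused by stimulation is a real active-sham difference. What is in doubt is its meaning.

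It can also be said that the mechanistic aim covers how stimulation modulates cortical excitability, so a recent effect is partly of interest; that fatigue from the procedure itself is balanced, since sham keeps the same targets and duration; that a condensed article often leaves visit windows to a fuller document; and that the EEG is declared exploratory.

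Most of this stands and limits the severity. It does not remove the point. The article does state the timing, and it conflicts with its own table. The declared use of P300 goes beyond acute excitability to the therapeutic effect and biomarkers of response. The limitations paragraph does not mention the timing of the recording.

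**Conclusion.** The point holds for P300 only. The contradiction between the Study design text and Table 1 is certain. The confounding depends on which of them governs. Under Table 1 it is complete, because a single post-treatment recording carries both effects. Under the text, the T1 contrast is still mixed, but T2 and T3 would show what lasts.

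The conclusion assumes that a session has some short-lived effect on P300, which the protocol's recovery rationale suggests but does not quantify, and that the tilted sham coil produces no comparable effect. Because the size is unknown and the outcome is exploratory, severity is low to moderate. The primary outcome and the other ratings do not need to move.

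**What to change.** For P300 only:

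- In the Study design section and Table 1, give the T1 EEG its own window, the same in both arms. It should open no sooner than the protocol's own 3-hour between-session interval after the last session, preferably on the next available day and at the same time of day as the baseline EEG.
- Record the time from last pulse to EEG for every participant, since the 3 hours is not a measured washout.
- State in both places whether P300 is recorded at T2 and T3. If it is, use those recordings to distinguish lasting from acute change. If it is not, say that a T1 difference cannot be attributed to the course alone, and limit the biomarker conclusion accordingly.

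The cost is an EEG some hours to a day later, possibly with one more attendance. As treatment is on weekdays, a course ending on a Friday could mean a weekend delay. No additional staff or new procedure is needed. The stimulation schedule and the timing of HAMD-17, BDI-II and C-SSRS stay as they are.
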